#### Plans to promote participant retention and complete follow-up {18b}

Participants who deviate from the protocol will not be withdrawn from the trial. Participants who withdraw from the trial nominate the degree to which they withdraw (i.e., whether they withdraw from active data collection ± passive data collection such as hospital records). To avoid losing participants to follow-up, contact information of a friend or family member will be requested as a back-up contact in case of difficulty in contacting the participant. Provision of a contact is not mandatory and will not result in exclusion from the trial.

#### Data management {19}

All participant characteristic and outcome data are entered directly into REDCap (Research Electronic Data CAPture—Vanderbilt University, hosted at Queensland University of Technology) by the research nurse and the participants through self-administered online survey. To ensure data quality, the database is designed with branching logic, data validation, and range checks for data values, where possible.

All source data, clinical records, and laboratory data relating to the study will be archived at the clinical site as appropriate for 15 years after the completion of the study. All data will be available for retrospective review or audit. No study document will be destroyed without prior written agreement between the responsible organization and the investigator. If the investigator wishes to assign the study records to another party or move them to another location, he/she must notify the responsible organization in writing of the new responsible person and/or the new location.

#### Confidentiality {27}

Data on potential participants is recorded, including reasons for ineligibility or refusal to participate. Participants are only identified by a unique participant study number on the case report forms and other study documents. Other study-related documents (e.g., signed consent form, participant log) are kept in strict confidence by the investigator.

Participants are informed that data is held on file by the responsible organizations and that these data may be viewed by staff including the study project manager and by external auditors on behalf of the responsible organizations and appropriate regulatory authorities (to include reviewing Human Research Ethics Committee (HREC) and the Research Governance Officers). Participant data in publications and conference presentation reports will only be presented in aggregated form. All participant data will be held in strict confidence.

#### Plans for collection, laboratory evaluation, and storage of biological specimens for genetic or molecular analysis in this trial/future use {33}

Not applicable. There is no collection of biological specimens in the current trial.

## Statistical methods

### Statistical methods for primary and secondary outcomes {20a}

Descriptive statistics will be used to report on feasibility and process-related elements (e.g., recruitment, intervention, retention rates) as well as clinical and resource outcomes. Preliminary effect size estimates for patient and resource use outcomes will be calculated following intention-to-treat principles using linear mixed models. Models will include group, time, and their interaction and be adjusted by diagnosis and age. Balance of demographic variables between usual care and intervention group will be investigated using chi-square and *t* test and will be included in the model if found to be both significantly associated with the outcome and confounding the intervention. Assumptions of all models (normality, linearity, homoscedasticity) will be examined using the residuals of the model and will be described using mean, median, skewness, kurtosis, and plots such as histograms and QQ-plots. If assumptions are violated, models will be either bootstrapped or log transformation as appropriate.

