### Eligibility criteria {10}

Due to the varying follow-up requirements for patients with lymphoma, the study population consists of two groups of patients who require two distinct follow-up pathways. Group one (post-treatment follow-up) consists of patients with a histopathologically confirmed diagnosis of aggressive or indolent lymphoma in the acute post-treatment phase (i.e., within 3 months of completion of chemotherapy). Group two (observation follow-up) consists of patients with a histopathologically confirmed diagnosis of indolent lymphoma followed up in the surveillance clinic who are at least 2 years post-treatment or treatment naïve. In addition to meeting one of the group descriptions above, participants must also meet all of the following criteria to be eligible for inclusion: ≥ 18 years of age, have an Easter Cooperative Oncology Group (ECOG) performance status < 2, be an ambulatory outpatient at the time of recruitment, be able to nominate a GP or GP clinic to be involved in their follow-up, have access to a telephone, and be able to speak and read English. Patients meeting any of the following criteria are excluded: the presence of severe mental, cognitive or physical conditions that would limit the patient’s ability to participate as per treating clinician, lymphoma not in remission (applicable for group 1 only), and patients receiving maintenance treatment.

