### Assignment of interventions: allocation

#### Sequence generation {16a}

Permuted block randomization will be conducted to assign participants to the control or intervention arms (Fig. 1). To ensure equal distribution of patients with different follow-up schedules, patients will be stratified by diagnosis (NHL vs HL) and follow-up pathway (group one: post-treatment vs group two: surveillance clinic).

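### Follow-up pathway stratifies the randomisation but has no route into the mixed models, so if recovery differs by pathway the group x time intervals are somewhat too wide

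*Protocol article*

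**What the plan says.** Under Sequence generation {16a}, the article says "Permuted block randomization will be conducted to assign participants to the control or intervention arms" and that "patients will be stratified by diagnosis (NHL vs HL) and follow-up pathway". The reason given is to spread patients with different follow-up schedules evenly over the arms.

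Under Eligibility criteria {10}, "the study population consists of two groups of patients who require two distinct follow-up pathways". Group one is "in the acute post-treatment phase (i.e., within 3 months of completion of chemotherapy"). Group two has indolent disease and is either two or more years past treatment or has never been treated.

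Under Statistical methods for primary and secondary outcomes {20a}, the model is fixed: it takes group, time and the group x time term, and is to "be adjusted by diagnosis and age". Demographic variables are compared between arms, and any such variable "will be included in the model if found to be both significantly associated with the outcome and confounding the intervention". Table 4 expresses most patient-reported outcomes, FACT-Lym among them, as change over baseline, 6 and 12 months compared between groups.

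**The concern.** The design uses two stratification factors. The analysis keeps one of them (diagnosis), drops the other (pathway) and adds age, which was not stratified on. No reason is given.

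The screen for extra covariates does not repair this. Pathway is a clinical grouping, not a demographic variable. Because stratification balances it over the arms, it would also not be expected to show up as a confounder.

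When a balanced factor that predicts the outcome is left out, its variation stays in the residual. The treatment estimate is still unbiased, but the model does not credit the balance that the randomisation achieved, so the reported standard error is too large. At stake is the precision of the early effect-size estimates that the trial is partly meant to supply (Sample size {14}). Its feasibility results are not affected.

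**Working it through.** **Stated figure.** There is none to reproduce. Sample size {14} sets 30 patients per arm by pilot-study convention, with no power, effect size or SD.

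**Inputs from the article.** 30 per arm, 1:1; visits at baseline, 6 and 12 months; model terms group, time, group x time, diagnosis and age.

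**Assumed inputs.** Outcome SD 1 at each visit within pathway; pathway share p = 0.5; correlation between visits r = 0.5 to 0.7; d = difference between pathways in 12-month change = 0.5 to 0.8 SD. None of these is in the documents.

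**(a) Two-visit change score.** The variance of change is 2(1 - r). Leaving pathway out adds p(1 - p)d² = 0.25d². Hence

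SE without pathway / SE with pathway = sqrt(1 + 0.25d² / (2(1 - r))).

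| d | r = 0.5 | r = 0.7 |
|---|---|---|
| 0.5 | sqrt(1 + 0.0625/1.0) = 1.03 | sqrt(1 + 0.0625/0.6) = 1.05 |
| 0.8 | sqrt(1 + 0.16/1.0) = 1.08 | sqrt(1 + 0.16/0.6) = 1.13 |

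The excess is 3-13%. A simulation of this analysis (n = 60, stratified 1:1 allocation, 4000 runs per setting, pathway share 30% or 50%) gave the same 3-13%. Nominal 95% intervals covered 95.5-97.3% without pathway and 94.8-95.2% with it.

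**(b) Three-visit random-intercept model.** This is closer to the stated plan, although the article does not name the covariance structure. A constant pathway difference in level goes into the patient intercept and does not touch the group x time contrast. Only divergence over time reaches the within-patient residual, whose variance is 1 - r. Suppose the pathways diverge linearly, by 0, 0.5d and d at the three visits. The squared deviations of (0, 0.5, 1) about their mean sum to 0.5. Spread over two within-patient degrees of freedom, that is 0.25. The added variance is 0.25 x 0.25d² = 0.0625d², so

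ratio = sqrt(1 + 0.0625d² / (1 - r)).

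| d | r = 0.5 | r = 0.7 |
|---|---|---|
| 0.5 | sqrt(1 + 0.0156/0.5) = 1.016 | sqrt(1 + 0.0156/0.3) = 1.026 |
| 0.8 | sqrt(1 + 0.04/0.5) = 1.039 | sqrt(1 + 0.04/0.3) = 1.065 |

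The excess is about 2-6%. The relative excess in variance is half that in (a), because the residual variance is pooled over three visits.

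**(c) Fitted mixed models.** Data were simulated for n = 60, three visits, intraclass correlation 0.6 and a 50:50 split, with 40 replicates per setting. That is too few to judge coverage, so only the model-based SEs of the 12-month group x time term are used.

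| d | SE without pathway / SE with pathway x time |
|---|---|
| 0 | 1.00 |
| 0.3 | about 1.01 |
| 0.5 | 1.02 |
| 0.8 | 1.06 |

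Adding pathway as a main effect only left this SE unchanged (ratio 1.000).

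**On the outcome scale.** In (c) with d = 0.8 and no baseline difference between pathways, the SEs were 0.242 without pathway and 0.229 with pathway x time. The 95% half-widths are 1.96 x 0.242 = 0.47 SD and 1.96 x 0.229 = 0.45 SD.

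**The case against.** The strongest reply is that little turns on this. The error is conservative, the estimate is unbiased, the article says that hypothesis testing is not the aim, and feasibility outcomes are reported descriptively. A few percent on an interval from 60 patients is small beside its sampling error. All of that stands, and it limits the weight of the point. It does not explain why one stratification factor is modelled and the other is not.

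A second reply is that the analysis plan may add pathway. But the section does not leave the covariates open: it lists them and states the one rule for adding more. As written, that rule excludes pathway.

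Three stronger readings are tempting, and the documents do not support them:

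- **Pathway is the main driver of recovery.** The group definitions make different trajectories plausible, but no section reports outcomes by pathway, and the stated reason for stratifying is the follow-up schedule.
- **The SD carried into the definitive trial will be inflated.** The article does not say that an SD from these models will size that trial. If that trial enrolled the same mix and used the same analysis, the pooled SD would be the relevant one.
- **Any omitted stratification factor widens these intervals.** For a contrast in change, a stable difference in level does not. Only divergence over time does.

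**Conclusion.** The mismatch between the randomisation and the model is plain on the page, and the direction of its effect is settled: intervals that are too wide or unaffected, never biased estimates. The size is modest and conditional. Under the assumptions set out above, the planned kind of model overstates the SE by about 2-6%. The figure of 13% needs a two-visit change-score analysis together with the largest assumed difference and correlation. If the pathways change in parallel there is no loss. The point is worth correcting because it is easily put right and makes the analysis follow the design. It does not threaten the trial's conclusions on feasibility.

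**What to change.** In Statistical methods for primary and secondary outcomes {20a}, add follow-up pathway and pathway x time to the pre-specified fixed effects, alongside diagnosis and age, and take pathway as recorded at randomisation. Both terms are needed, since the main effect alone would not narrow the group x time interval.

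With three visits and time as a factor, the cost is one parameter for pathway and two for pathway x time, three in all. It takes one sentence of text and no new data, because pathway must already be known to randomise each patient.

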**Methods:**

We describe a protocol for a phase II, randomized controlled trial with two parallel arms and a 1:1 allocation. Sixty patients with Hodgkin’s and non-Hodgkin’s lymphoma will be randomized to usual specialist-led follow-up care (as determined by the treating hematologists) or a shared follow-up care intervention (i.e., GOSPEL I). GOSPEL I is a nurse-enabled, pre-specified shared care pathway with follow-up responsibilities shared between cancer center specialists (i.e., hematologists and specialist cancer nurses) and GPs. Outcome measures assess feasibility as well as a range of patient-reported outcomes including health-related quality of life as measured by the Functional Assessment of Cancer Therapy—Lymphoma, patient experience of care, symptom distress, comorbidity burden, dietary intake, physical activity behaviors, financial distress/interference, and satisfaction of care. Safety indicators including hospital admission and unscheduled lymphoma clinic visits as well as process outcomes such as intervention fidelity and economic indicators will be analyzed.

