### Participant timeline {13}

### Sample size {14}

In this pilot study, we will recruit 30 patients per arm in order to provide initial insights into the intervention feasibility and protocol as well as preliminary effect size estimates. The aim of this study is not hypothesis testing; the power level is therefore not a valid consideration for sample size [29, 30]. The sample size for this study (*n* = 60) falls within the range of sample size recommendations for pilot studies of this nature [29, 30].

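### Beyond diagnosis and age, demographic covariates enter each outcome's model by tests on the trial's own data, while the stratification factor follow-up pathway is left out

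*Protocol article*

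**What the plan says.** Statistical methods {20a} of the Protocol article has a fixed part and a conditional part.

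- **Fixed:** "Models will include group, time, and their interaction and be adjusted by diagnosis and age".
- **Conditional:** "Balance of demographic variables between usual care and intervention group will be investigated using chi-square and" t tests, and a variable "will be included in the model if found to be both significantly associated with the outcome and confounding the intervention".

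The article gives no candidate list, no significance level and no definition of *confounding*. A statistical analysis plan may supply these, so their absence is not the point. The selection rule itself is stated.

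Three other places matter:

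- **Sequence generation {16a}** uses permuted blocks stratified by diagnosis and by follow-up pathway (post-treatment or surveillance clinic). Of these two factors, {20a} names only diagnosis as a covariate.
- **Concealment mechanism {16b} and Implementation {16c}** describe sequentially numbered, opaque, sealed envelopes and a sequence made by someone outside recruitment and data collection.
- **Sample size {14}** says "we will recruit 30 patients per arm" and names preliminary effect sizes as one product of the pilot.

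**The concern.** With concealed random allocation, a baseline difference between arms can only be chance. A chi-square or t test of balance therefore tests a null hypothesis already known to be true, and its result does not show whether a variable is worth adjusting for. That depends on how strongly the variable predicts the outcome.

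The second condition uses the trial's own outcome data to choose the model that then estimates the effect, and the reported standard error treats that model as if it had been fixed in advance. The rule also runs outcome by outcome. Table 4 lists nine outcome domains and {20a} adds resource use, so effect sizes shown side by side could be adjusted for different variables.

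At stake are the preliminary effect sizes that are meant to inform the definitive trial. Meanwhile a factor used in the randomisation is absent from the fixed part of the model.

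**Working it through.** The plan derives no figure on this point, so there is nothing to reproduce. What follows is illustration.

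**From the documents:** 30 per arm, 60 in total, 1:1 allocation.

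**Assumed, not in the documents:** a 5% test level; the number of candidate variables; their correlation r with the outcome; the meaning of *confounding*.

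**1. Chance imbalance.** For k independent variables, P(at least one significant) = 1 − 0.95^k. This is 1 − 0.95^6 = 0.265 for k = 6 and 1 − 0.95^10 = 0.401 for k = 10. It is the chance of a significant balance test, not of a changed model.

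**2. Imbalance needed for significance.** t(0.975; 58) × √(2/30) = 0.517 SD.

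**3. Passing the outcome test.** For r = 0.3 and n = 60, atanh(0.3) × √57 = 2.34, so power = Φ(2.34 − 1.96) ≈ 0.65. For r = 0.2 it is 0.33, and for r = 0.5 it is 0.99.

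**4. Both tests significant.** For one variable with r = 0.3, assuming independent tests, 0.647 × 0.05 = 0.032.

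**5. Simulation.** 8000 runs, 30 per arm, no true effect, six candidates of which two have correlation r with the outcome, one follow-up, ordinary least squares. Rule A adds a candidate if the outcome association and the balance test are both significant. Rule B adds it if the association is significant and the effect estimate changes by more than 10%. *Pre-specified* always adjusts for the two variables.

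| | r = 0 | r = 0.3 | r = 0.5 |
|---|---|---|---|
| Any covariate added, A | 1.7% | 7.2% | 10.4% |
| Any covariate added, B | 21% | 83% | 98% |
| SD of effect, unadjusted | 0.259 | 0.258 | 0.260 |
| SD of effect, A | 0.258 | 0.253 | 0.242 |
| SD of effect, B | 0.257 | 0.241 | 0.191 |
| SD of effect, pre-specified | 0.263 | 0.240 | 0.190 |
| Mean model SE, A | 0.257 | 0.257 | 0.255 |
| Mean model SE, B | 0.255 | 0.240 | 0.194 |
| Type I error, A | 0.052 | 0.046 | 0.036 |
| Type I error, B | 0.051 | 0.046 | 0.043 |

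Step 4 agrees with the table: 2 × 0.032 + 4 × 0.05 × 0.05 = 0.074, against 7.2% simulated.

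**6. Loss under rule A.** 0.253 / 0.240 = 1.05, so the SD is about 5% larger than under pre-specification at r = 0.3. At r = 0.5, 0.242 / 0.190 = 1.27, about 27% larger. The model SE is too large: 0.255 / 0.242 = 1.05 at r = 0.5 and 0.257 / 0.253 = 1.02 at r = 0.3.

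**7. Loss under rule B.** 0.241 against 0.240, and 0.191 against 0.190: almost none. What remains is a model that changes often, in 21% of trials even when no candidate predicts the outcome.

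**Limit of the simulation.** It has a single follow-up and no baseline score. If baseline is a level of time in the planned model, a covariate that is constant over time and enters only as a main effect cancels from the group-by-time contrast when data are complete. The losses above therefore apply most directly to comparisons at one time point, such as satisfaction of care, and are likely to be smaller for a group-by-time contrast.

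**The case against.** The strongest reply is that the rule rarely matters. The fixed model already holds diagnosis and age. If *confounding* means a significant balance test, that fixed model is what would run in about 90% of trials or more. If it means a change in the estimate, prognostic variables mostly do enter and precision is kept. Letting in an imbalanced variable that predicts the outcome is not a harm in itself. This is a 60-patient feasibility pilot, and the article says "The aim of this study is not hypothesis testing; the power level is therefore not a valid consideration for sample size".

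Much of this stands, and it limits the size of the point. The sentence on hypothesis testing explains why power did not set the sample size; it does not by itself contradict a baseline check. What does not fall away is that the choice of model depends on outcome data, can differ between outcomes, and is not reflected in the standard error. Both readings of *confounding* share this fault, so defining the word in an analysis plan would not cure it.

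A reader might infer three stronger things that the documents do not support:

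- **That no covariate is pre-specified.** Diagnosis and age always are.
- **That the model has a 26–40% chance of being altered.** That is the chance of any significant imbalance among 6 to 10 variables, and the rule also requires an association with the outcome.
- **That a variable with r = 0.3 would be included only about 3% of the time.** This holds only if *confounding* means a significant balance test.

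**Conclusion.** The point holds in a limited form. For demographic variables other than age, {20a} lets chance imbalance and the trial's own outcome data choose the adjustment, and it leaves follow-up pathway out of the model although the randomisation is stratified by it.

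The consequence is some lost precision and a slightly miscalibrated standard error in the preliminary effect sizes. Under the balance-test reading, with two covariates assumed to correlate 0.3 or 0.5 with the outcome, the SD of the effect is about 5% or 27% larger than under pre-specification, and the model SE is about 2% or 5% too large. Under the change-in-estimate reading the precision loss is negligible and the instability of the model is the main complaint.

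It might be inferred that the rule produces false positives. The simulation does not show this: type I error was 0.036 to 0.052 under the two rules. The effect of omitting follow-up pathway was not quantified, because the document gives no figure for how strongly it predicts any outcome.

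**What to change.** In {20a}, delete the one sentence that holds the balance tests and the selection rule. Replace it with a statement to this effect: all models adjust for diagnosis, follow-up pathway and age, plus any prognostic variable named before unblinding; the same set is used for every outcome; baseline characteristics are reported by arm descriptively, without tests.

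Baseline score needs separate handling. For outcomes in the group-by-time model, keep it as a modelled time point. Use it as a covariate only where follow-up scores alone are modelled and a baseline measure exists. Satisfaction of care is collected only at 12 months (Tables 3 and 4), so it has none. Entering baseline both as a time point and as a covariate would use it twice.

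The cost is one sentence of text and one or two degrees of freedom. In the simulation, two covariates of no prognostic value raised the mean model SE from 0.257 to 0.262, about 2%. The sample size of 60 does not change.
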